### Consent

Valid implied consent is assumed for participation, an approach used in two other recent trials in TB and HIV screening in London [12, 13] . All eligible patients are given a patient information sheet (PIS) in English and six other languages.

Eligible patients are asked for verbal consent to access their data which will be recorded in their electronic patient records. The PIS explains how patient data is collected and how patients may opt out of the study.

Our approach to consent was formally approved in our ethics application (see “Ethics approval”).

### Recruitment

It is expected that most eligible patients will be offered testing for LTBI at a “new patient check”, usually performed by a health care assistant or qualified nurse shortly after a patient registers with a GP practice. Patients will be given a PIS about the CATAPuLT trial when offered testing for LTBI.

The trial will also recruit eligible patients who are already registered with a GP. They will be given a PIS when offered an IGRA blood test. Eligible IGRA-positive patients tested prior to the trial opening who have not yet had a follow up appointment will be given a PIS and managed as per the arm of their GP practice. Eligible IGRA-positive patients tested prior to the trial opening who have had a follow up appointment but no prescription for treatment issued may be given a PIS and managed as per the arm of their GP practice. This group will be treated as a separate cohort and analysed separately from the main trial.

Cluster-level data about the number of positive tests recorded at each site will be monitored to ensure that all eligible patients are asked for consent to share their data with the trial team.

### Randomisation

Twenty GP practices were initially recruited and randomised, but after participant recruitment rates were lower than expected further practices were randomised across three further phases as practices became ready to join the trial. In the initial phase, 20 GP practices were stratified for randomisation by the cross-classification of two binary factors based on practice size and number of IGRA positives identified previously.

There were three further phases of randomisation for practices 21–22, 23–29 and 30–34 respectively. Of these, the randomisation of practices 23–29 was stratified by the number of IGRA positives and in the other phases randomisation was unrestricted. Practices 23–29 were randomised with the allocation of 3 to one study arm and 4 to the other (determined at random). In the final phase the allocation was 2 to one study arm and 3 to the other, allocating 3 to the arm that was allocated only 3 in the third phase, to ensure an overall 1:1 allocation of 17 practices to each arm. At all phases and within all strata the randomisation was implemented through random permutation using STATA v15 (STATA Corporation, College Station, Texas, USA). Randomisation was conducted by the trial statistician (AC). Information about study sites can be obtained from the corresponding author or chief investigator.

### Blinding

Data collection and analysis will be unblinded due to the nature of the intervention, cluster level randomisation and different data collection systems for the two study arms.

### Data collection methods and management

#### Study tools

Patient satisfaction and adverse effects will be assessed using non-validated questionnaires. Patient knowledge about LTBI will be assessed using a non-validated questionnaire adapted from two previous studies [14, 15]. The MARS-5 adherence questionnaire has not been validated for use in LTBI [11]. The Isoscreen® point of care test for metabolites of isoniazid (GFC Diagnostics, Oxfordshire, UK) has been validated in small prospective studies with a sensitivity of greater than 90% and a specificity of greater than 95% [16–18].

#### Data collection and management

Patient data will be entered electronically by the patients’ usual care team. All data collection will use purpose-built electronic management templates, adapted those developed for the national LTBI screening programme by the Clinical Effectiveness Group, Queen Mary University of London for Public Health England (PHE) [19]. Data will be managed and stored in accordance with local and national information governance specifications.

### Analysis

All analyses will be conducted on an intention-to-treat basis. The analysis will include all eligible participants regardless of how well the GP practice followed the study protocol or how well the participant complied with their treatment plan. The analysis will exclude any patients however who have withdrawn from the trial and specified they do not wish their data to be analysed.

Some outcomes are only applicable for certain subgroups. The primary outcome is defined only for patients who accept treatment. Patient satisfaction is only defined for patients who are still under care at 2 months, when the satisfaction questionnaire is administered. The MARS-5 and isoniazid metabolite urine testing adherence measures are only applicable at times when the patient is still taking treatment, i.e. not stopped due to adverse effects or by patient choice/withdrawal from the trial.

The primary outcome will be analysed using a logistic regression model. Results will be reported as odds ratios (OR) for the intervention compared to control with their corresponding 95% confidence intervals (CI) and two-sided *p*-values. The ICC for the primary outcome will be reported. Similarly, across the secondary outcomes treatment effect estimates will be presented with 95% confidence intervals based on regression models, using binary logistic regression, ordinal logistic regression or linear regression as appropriate. Regression models will include random intercept effects for GP practice.

Adjusted effect measures are considered the primary effect measures; unadjusted measures will also be reported. We will adjust the analyses for practice size and number of previous IGRA positives, our stratification factors, and selected pre-determined participant factors considered predictive of treatment completion.

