In the intervention arm, the GP excludes active TB, and offers treatment for LTBI. The patient is asked to select one accredited community pharmacy for treatment. The borough has 16 community pharmacies that have been trained and accredited to provide LTBI treatment. Treatment is initiated and monitored by a community pharmacist. At their initial visit, the community pharmacist will counsel the patient about LTBI treatment. The patient is then issued with a 1 month supply of medication and asked to attend for liver function tests (LFTs) after 2–4 weeks. The patient attends the pharmacy at the end of each of the 3 months of treatment to assess adherence and adverse effects. In the control arm, the TB clinician and TB nurse mirror the role of the GP and community pharmacist respectively. Prior to starting treatment, a questionnaire will be used to assess knowledge about LTBI.

Follow up is identical in trial both arms: at the end of each month of treatment adherence is assessed using a pill count (or self-report if the patient fails to attend with their tablets), and the Medication Adherence Report Scale (MARS-5), a set of 5 statements about common patterns of adherence rated on a 5-point Likert scale (1 = always, 2 = often, 3 = sometimes, 4 = rarely, and 5 = never) [11]. At the first and second visits, urine is tested for metabolites of isoniazid (Isoscreen®, GFC Diagnostics, Oxfordshire, UK). At the second visit, the patient completes a satisfaction questionnaire. Prior to starting treatment, a questionnaire will be used to assess knowledge about LTBI. See Table 1.

**Table 1 Tab1:** Timetable of assessments in the CATAPuLT Trial. For Urine testing a minimum of two urine tests should be performed during the 3 months of treatment. These should be done at the review visit for months 1 and 2 of treatment, although the second may be done at the final visit instead if the patient was unable to provide a sample at either of the earlier visits, or additionally at the final visit if there are concerns about adherence, *LFTs Liver function test, **INH Isoniazid

Assessment Tool	Day 0	Day 15	Day 30	Day 60	Day 90
Questionnaire (Understanding and knowledge of LTBI)	X				
Blood tests for LFTs*		X			
Pill count / MARS5 tool			X	X	X
Questionnaire (adherence/ adverse effects)			X	X	X
Urine test (Colour and INH **metabolites)			X	X	
Patient satisfaction questionnaire				X	

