### Outcomes

#### Primary outcome –treatment completion

Completion of at least 90% of prescribed therapy as assessed by pill count. Where a patient fails to bring their medication, information will be obtained by patient report. Treatment completion will be assessed at the final patient review, approximately 3 months after treatment is commenced. To avoid bias, an independent researcher, blinded to allocation, will verify treatment completion where there is uncertainty. This outcome is defined for IGRA positive patients who accept treatment.

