#### Secondary outcomes

Proportion of participants completing < 80, 80–89.9, ≥90% of antibiotic dosages based on pill count.Treatment adherence assessed using the five-point adherence questionnaire (MARS5 tool), prescription collection and a point-of-care urine testing for metabolites of Isoniazid (Isoscreen) at monthly intervals.Treatment acceptance assessed by calculating the proportion of eligible patients that accept therapy; this is defined as those initiating treatment and attending TB clinics and community pharmacies on at least one occasion.The number of patients on treatment having adverse events including DILI leading to discontinuation of treatment or hospitalisation. Safety of treatment will be assessed every month by the pharmacist in primary care and by the TB nurse in secondary care.The incidence of active TB occurring within 2 years after enrolment. TB incidence in the intervention and control group will be compared and there will be a sub-group analysis to evaluate the effect of the intervention in those who did or did not complete treatment. This will be performed through matching the study population with the national Enhanced TB Surveillance System, where information on all reported TB cases nationally are recorded.Assessment of patient satisfaction.Evaluation of cost-effectiveness of LTBI treatment in primary care compared to secondary care.

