### Patient and public involvement

Increasing patient choice and improving patient experience underlie the central hypothesis of the trial. The intervention enables patients to select an accredited pharmacy most convenient for them geographically and to attend outside office hours and at weekends in contrast to the specialist TB service. Prior to the design of the trial interviews were conducted with patients who had been treated for LTBI in the pilot service in Newham. The trial is supported by the chair of the “Patient Panel” at Barts Health NHS Trust and the local branch of Healthwatch, the independent consumer champion for health and social care in England. All questionnaires in the trial were piloted with eligible patients.

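### The primary completion analysis counts only patients who accept treatment, which is decided after randomisation in the allocated setting, so it is not the intention-to-treat comparison the article declares

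*Protocol article*

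**What the plan says.** The Analysis section of the protocol article opens with "All analyses will be conducted on an intention-to-treat basis" and continues: "The analysis will include all eligible participants regardless of how well the GP practice followed the study protocol". Its next paragraph notes that some outcomes apply only to certain subgroups and states: "The primary outcome is defined only for patients who accept treatment". The primary outcome definition agrees: "This outcome is defined for IGRA positive patients who accept treatment".

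Acceptance is also listed under Secondary outcomes: "Treatment acceptance assessed by calculating the proportion of eligible patients that accept therapy". It is defined there by what the patient does in the allocated service: "this is defined as those initiating treatment and attending TB clinics and community pharmacies on at least one occasion".

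On timing and setting, practices are the randomised units (Randomisation) and data collection and analysis are unblinded (Blinding). Setting/intervention says: "In the intervention arm, the GP excludes active TB, and offers treatment for LTBI". In control, the patient is referred and the TB clinician takes that role.

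The Sample size section inflates the number needed for loss to follow-up and non-acceptance together, so non-acceptors are planned for as patients who do not provide the primary outcome.

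**The concern.** Randomising practices makes the two groups of IGRA-positive patients comparable. It does not make the two groups of acceptors comparable, because each patient decides whether to start knowing which setting is on offer. If one setting draws in more hesitant patients, its completion rate among starters falls for that reason alone. If the other setting loses hesitant patients between referral and first attendance, its rate rises.

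The Missing data section sharpens this. A patient who starts and then withdraws without collecting all prescriptions counts as a failure, while a patient who never starts is not counted at all. A setting that brings a hesitant patient as far as one visit can therefore score worse than a setting that never sees that patient.

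The Background justifies the trial by low completion along the whole cascade of care, and the Discussion says the results will inform national policy. A reader told that the analysis is intention-to-treat would take the primary odds ratio as the effect of the model of care on patients offered it. As written, it is not that effect.

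**Working it through.** **The plan's own figures.** The Sample size section predicts completion of 70% in secondary care and 85% in primary care. It asks for 442 patients providing the primary outcome and inflates this by 30%: 442 × 1.30 = 574.6, against a stated 576. The first-phase figure follows the same rule: 780 × 1.30 = 1014. This confirms that non-acceptors are planned for as missing from the primary outcome. How 442 was derived does not bear on this point.

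**Inputs.** From the article: completion of 70% (control) and 85% (intervention), ICC 0.05, coefficient of variation of cluster size 0.5, 34 practices, target 576. Assumed, because the article gives none: acceptance a0 (control) and a1 (intervention), and completion e among patients who accept only in the intervention setting.

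**Formulas.** Suppose a1 > a0 and everyone who would accept in control would also accept in the intervention. Let c0 and c1 be completion, under control and intervention, in patients who would accept in either setting.
- Acceptors, intervention: [a0·c1 + (a1 − a0)·e] / a1
- Acceptors, control: c0
- All eligible: acceptance × completion among acceptors

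**Case A: the article's 85% v 70%, acceptance 90% v 70%, e = 50%.**
- Acceptors: (0.70 × 0.85 + 0.20 × 0.50)/0.90 = 0.695/0.90 = 77.2% v 70.0%, difference +7.2 points
- All eligible: 69.5% v 0.70 × 0.70 = 49.0%, difference +20.5 points

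The acceptor difference of 7.2 matches neither the all-eligible effect (20.5) nor the effect in those who would accept in either setting (85 − 70 = 15). The sign is the same throughout.

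**Case B: same acceptance and e, but no effect among those who would accept in either setting (c0 = c1).**
- At 70% in both arms, acceptors: (0.70 × 0.70 + 0.20 × 0.50)/0.90 = 65.6% v 70.0%, −4.4 points. All eligible: 59.0% v 49.0%, +10.0 points.
- At 85% in both arms, acceptors: 77.2% v 85.0%, −7.8 points. All eligible: 69.5% v 59.5%, +10.0 points.

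**Case C: acceptance lower in the intervention arm, with 85% v 70% observed among acceptors.** The all-eligible difference turns negative when a1 × 0.85 < a0 × 0.70, that is, when a1/a0 < 0.70/0.85 = 0.82. With acceptance of 70% (intervention) and 90% (control): 0.70 × 0.85 = 59.5% v 0.90 × 0.70 = 63.0%, −3.5 points, against +15 among acceptors.

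**Case D: equal acceptance, with 85% v 70% among acceptors.** The sign cannot change; the difference shrinks in proportion to acceptance. At 70%: 59.5% v 49.0%, 10.5 points. At 77%: 65.5% v 53.9%, 11.6 points.

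**Power of an all-eligible analysis in Case D.** Assume that all 576 contribute and that the ICC of 0.05 carries over. Mean cluster size is 576/34 = 16.94, and the design effect is 1 + [(1 + 0.5²) × 16.94 − 1] × 0.05 = 2.01. The effective number per arm is 288/2.01 = 143. Two-sided 5% power is about 43% at 70% acceptance and about 51% at 77%.

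**The case against.** The restriction is open and consistent. It appears in both the outcome definition and the Analysis section, which qualifies its own opening by saying that some outcomes apply only to subgroups, and the sample size allows for it. Acceptors are still analysed by allocation and regardless of compliance. Acceptance is reported as a secondary outcome with an interval, so a large gap between arms would be visible and the two rates could be multiplied. This stands as far as it goes: the population is a deliberate choice and part of the safeguard exists. But disclosure does not turn the comparison into intention-to-treat, and multiplying two rates gives no adjusted, cluster-aware estimate, interval or test.

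Three stronger readings are tempting, and the article does not support them.

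- **That the primary result will have the wrong sign.** Reversal needs either no effect among those who would accept in either setting (Case B), which drops the article's own prediction, or clearly lower acceptance in primary care (Case C). With the article's completion rates and higher acceptance in primary care (Case A), there is none.
- **That the intervention is intended to change acceptance.** Patient and public involvement says "Increasing patient choice and improving patient experience underlie the central hypothesis of the trial", which makes an effect on starting plausible. No direction or size for acceptance is stated; the only predicted effect is on completion.
- **That no all-eligible analysis is planned.** The article states none. The full protocol (version 8, per Ethics approval) and any analysis plan are not shown and may hold one.

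A further objection bears on the remedy. Eligibility is confirmed by a medical assessment after the IGRA, done by the GP in one arm and the TB clinician in the other. Someone who never attends has unknown eligibility, so the all-eligible denominator is itself partly formed after allocation. This is correct, and the fix has to allow for it.

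**Conclusion.** The concern holds in a limited form. It rests on a rule the article states, not on an omission: the primary population is fixed as acceptors, acceptance arises after randomisation inside the allocated setting, and the intention-to-treat sentence in the same section does not describe that analysis. If acceptance differs between arms, the primary odds ratio can be biased in either direction as a measure of what the model of care does for the patients offered it.

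The size cannot be fixed from the article, because it gives no acceptance rates by arm. Under the assumptions of Case A the effect is understated (+7.2 against +20.5 points) without a change of sign. If acceptance is equal, the sign is safe and only the scale differs. Opposite signs are possible but are not predicted by any figure in the article.

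**What to change.** 1. Reword the Analysis section to say that the primary estimand is completion conditional on acceptance, analysed by allocated arm, and that it is not a full intention-to-treat comparison.
2. Pre-specify a supportive analysis of at least 90% completion in all eligible IGRA-positive patients of the randomised practices. Use the same adjusted random-intercept logistic model and the denominator of the acceptance outcome, and count non-acceptors as not completed.
3. Add a sensitivity version that also includes IGRA-positive patients who never attended assessment, because eligibility is partly established within the allocated arm.
4. Report these beside the primary and acceptance results and interpret them together. No rule requiring them to agree in direction is needed.

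The primary outcome and the target of 576 stay as they are. The cost is a wording change, one or two extra models and a second completion figure to explain. The main denominator is already needed for the acceptance outcome; the sensitivity version also needs patient-level records for non-attenders. The supportive analysis would have low power if acceptance is similar in both arms (about 43% to 51% under Case D), so it should be read as an estimate with its interval and not as a second confirmatory test.

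### Randomisation phase restricted the allocation of all 34 practices but is missing from the primary adjusted model, which makes the analysis conservative if completion differs by phase

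*Protocol article*

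**What the plan says.** The Randomisation section of the protocol article explains that "after participant recruitment rates were lower than expected further practices were randomised across three further phases as practices became ready to join the trial". It continues: "There were three further phases of randomisation for practices 21–22, 23–29 and 30–34 respectively".

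The restrictions differed by phase:

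- The initial 20 practices were "stratified for randomisation by the cross-classification of two binary factors based on practice size and number of IGRA positives".
- Of the later phases, "the randomisation of practices 23–29 was stratified by the number of IGRA positives and in the other phases randomisation was unrestricted".
- For the third phase, "Practices 23–29 were randomised with the allocation of 3 to one study arm and 4 to the other". The fourth was split 2:3, with the larger share going to the arm that had received 3 in the third phase, so that each arm ended with 17 practices.
- Every phase and stratum was allocated by random permutation.

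The Analysis section makes the adjusted estimate primary, includes a random intercept for practice, and states "We will adjust the analyses for practice size and number of previous IGRA positives, our stratification factors". It adds pre-determined participant factors. Phase appears nowhere in that section.

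**The concern.** A trial that restricts its randomisation should reflect the restriction in its analysis. The plan accepts this principle, because it adjusts for the stratification factors on the ground that they are stratification factors. Those two factors cover only part of the scheme, while phase covers all of it. The sample size was reworked when the 14 later practices came in; the cluster-level covariates still match the initial 20-practice design.

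A difference between phases is plausible, though not shown. Later practices joined when they were ready. The Sample size section attributes variable cluster size to the 14 later practices. Residence criteria were widened from October 2017 to April 2018, after the first enrolment in January 2017. If completion does differ, that variation goes into the practice random intercept, and the model reports less precision than the design delivered. The trial was planned at 80% power with 34 clusters, so unused precision matters.

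**Working it through.** **1. Which restriction covered which practices (Randomisation section)**

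| Phase | Practices | Size | IGRA positives | Split |
|---|---|---|---|---|
| 1 | 20 | yes | yes | 10:10 (inferred) |
| 2 | 2 | no | no | 1:1 (inferred) |
| 3 | 7 | no | yes | 3:4 |
| 4 | 5 | no | no | 3:2, offsetting phase 3 |

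Phases 3 and 4 together give 3 + 3 = 6 and 4 + 2 = 6. To reach 17:17, phases 1 and 2 must total 11:11. The even splits shown for those two phases are the natural reading but are not stated. The full counts are then 10 + 1 + 3 + 3 = 17 and 10 + 1 + 4 + 2 = 17. Practice size restricted 20 of 34 practices, IGRA positives restricted 20 + 7 = 27, and phase restricted all 34. For 2 + 5 = 7 practices phase was the only restriction.

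**2. The plan's own figure**

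The protocol gives no figure for phase. The 221 per arm used below does reproduce. For 70% v 85%, two-sided 5% and 80% power, the uncorrected size is 120.47 per arm. With ICC 0.05, CV 0.5 and 17 practices per arm:

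120.47 × 0.95 / (1 − 120.47 × 0.05 × 1.25/17) = 205.4 per arm, or 12.08 per practice. Rounded up, 13 × 34 = 442.

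**3. Size of the overstatement**

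- Mean completion p = 0.775, so p(1 − p) = 0.174.
- Assumed practice SD of 0.5 logit. This is close to the planned ICC: 0.25 × 0.174 = 0.044 against 0.05.
- Assumed early-late difference d of 0.5 to 0.8 logit, roughly 0.174 × d = 9 to 14 percentage points.

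Variance of the arm difference with phase in the model:

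2 × [0.25 × 1.25/17 + 1/(221 × 0.174)] = 0.0888.

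With phase omitted, the between-practice variance gains (20/34)(14/34)d² = 0.242d²:

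- d = 0.5: 0.0888 + 2 × 0.242 × 0.25 × 1.25/17 = 0.0977, variance +10%, SE +5%.
- d = 0.8: 0.0888 + 2 × 0.242 × 0.64 × 1.25/17 = 0.1116, variance +26%, SE +12%.

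**4. Estimated or true variance?**

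Simulating the scheme on the logit scale (normal approximation, cluster-size CV about 0.5, later practices assumed smaller, 3,000 runs per setting):

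| d | True SD, without v with phase | Mean estimated SE, without v with phase | Type I error without phase |
|---|---|---|---|
| 0.5 | 0.290 v 0.290 | 0.303 v 0.292 | 4.0% |
| 0.8 | 0.291 v 0.289 | 0.322 v 0.293 | 2.8% |

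The true SD hardly moves; only the estimated SE does. The simulated overstatement of variance is (0.303/0.292)² = 1.08 and (0.322/0.293)² = 1.21, slightly below the formula.

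**5. Power with phase as initial 20 v later 14 (2,400 runs, t reference)**

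| d | Without phase | With phase |
|---|---|---|
| 0.5 | 82.3% | 84.2% |
| 0.8 | 79.3% | 83.8% |

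Part of these gains, 1.9 and 4.5 points, reflects slightly higher type I error. With no phase effect the two models gave 83.4% and 83.8%, so the added term cost nothing detectable.

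**6. A different coding, for direction only**

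Phase entered as four levels (3 df), beta-binomial outcomes with ICC 0.05, cluster-level regression, 4,000 runs per setting:

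| Spread between extreme phases | Type I error, without v with | Power, without v with |
|---|---|---|
| 0 points | 4.2% v 4.4% | 75% v 75% |
| 10 points | 4.4% v 5.1% | 73% v 75% |
| 20 points | 3.1% v 4.6% | 67% v 76% |
| 30 points | 1.5% v 4.6% | 58% v 77% |

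Bias was below 0.002 throughout. The larger spreads are assumed extremes and test a 3 df term, so they do not measure the gain from the fix below.

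**The case against.** The strongest reply is that the planned analysis is valid as it stands. Arms are near-balanced by phase, so the estimate is unbiased and the test errs towards caution. This stands. A reader might infer that omitting phase biases the odds ratio, leaves a damaging imbalance uncorrected, or raises the true sampling variance. The calculations support none of these.

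The phase effect is also assumed. The trial's whole target, 70% v 85%, is ln(0.85/0.15) − ln(0.70/0.30) = 0.89 logit, so d = 0.8 would make joining date nearly as influential as the intervention. All practices are in one borough, under one programme since 2014, with a shared TB clinic and 16 accredited pharmacies. Phase fixes when a practice joined, not when its patients were treated, so it is a loose marker of calendar time. This also stands, and is why the size is given as a range.

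Further, an ICC of 0.05 can be read as total between-practice variation that already contains any phase difference. Holding that total fixed, power without phase was 82.5%, 84.4% and 87.6% at d = 0, 0.5 and 0.8. On that reading, phase adjustment adds efficiency to the planned power; it does not repair a shortfall. The gain from including it remains about 2 to 4 points.

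The phases should not be described as separately balanced: the third and fourth were uneven and linked. Nor is the label in the Analysis section wrong. It names the only two stratification factors used, and the Randomisation section says where each applied.

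Finally, the analysis plan is not shown and might add phase. But the article itself lists the cluster-level covariates and leaves only participant factors open, and phase is not a participant factor.

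**Conclusion.** The point holds as one of efficiency and of consistency between design and analysis. Phase restricted allocation for every practice, was the only restriction for 7, and is absent from the stated primary model. If completion differs by phase, the reported standard error is too large. The overstatement is about 10% to 26% in variance (5% to 12% in SE) for an assumed difference of 0.5 to 0.8 logit with a practice SD of 0.5 logit, and including phase gains about 2 to 4 points of power. If there is no phase effect, nothing is lost either way. The figures rest on approximations to the planned mixed logistic model and on a phase effect that the documents do not give. They do not support calling the primary analysis biased or its type I error inflated.

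**What to change.** Before outcome data are analysed, add randomisation phase to the primary adjusted model as a fixed effect, coded initial 20 v later 14. Pooling the later phases is reasonable because one has only two practices and the third and fourth had linked allocations. Keep practice size and previous IGRA positives as covariates. If phase is left out deliberately, say why. The cost is one sentence and one degree of freedom; phase is already known for every practice and the required sample size does not change. Because the Blinding section says analysis is unblinded, a term added after outcomes are seen could look data-driven, so the timing matters.
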